### Measurement and outcome

2.4

The main study endpoints are disability, measured with the Pain Disability Index (PDI) and SFN-Rasch-built Overall Disability Scale (SFN-RODS), and health-related QOL, measured with the 12-item Short Form Survey (SF-12). Secondary endpoints are pain intensity, catastrophizing, mood (anxiety and depression) and SFN-related complaints, measured with Numeric Rating Scale (NRS), Pain Catastrophizing Scale (PCS), Hospital Anxiety and Depression Scale (HADS), and SFN-Symptom Inventory Questionnaire (SFN-SIQ). All the endpoints will be measured at several measurement points with daily and non-daily measurements (see Figure 1). The primary endpoint is based on the clinical improvement of the participants.

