### Daily measures

2.5

To measure the primary and secondary outcomes, participants will complete an electronic diary daily. An e-mail will be sent each day to remind participants to fill in the electronic diary. The diary is consisting of 9 questions about pain intensity, disability and physical activity, QOL and anxiety and depression. Table 2 shows an example of the diary questions.

**Table 2 tab2:** Overview of diary questions.

Pain intensity	How was your average pain during the day?
	How was your maximal pain during the day?
Pain diversity	How well did you succeed to handle your pain today?
Mood	If I have pain, I keep thinking how much I want the pain to stop
	I feel cheerful
	I score my life today
Activity	How hard was it (or would It be) to perform this activity?

Each question could be answered on a Likert scale 11 (0–10), in which 0 stand for not at all, and 10 for the most.

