### Statistical analysis

2.10

The baseline characteristics will be presented in means ± standard deviation, medians (interquartile range) or percentages, as appropriate, including age, sex, duration of SFN, use of pain medication, pain intensity, disability, and SFN-related diagnostic (such as skin biopsy outcome and outcome of quantitative sensory testing). The outcome of the questionnaires will be analyzed using SPSS (Version 27). Normality assumptions will be checked with the Shapiro–Wilk test. Normally distributed treatment effects variables will be analyzed with the paired student’s t-test. Non-normally distributed treatment effects variable will be analyzed with the paired Wilcoxon test.

The analysis of the daily dairy data will be conducted with the Shiny SCDA, which is a web application to analyze SCED studies (51, 84). Shiny SCDA, a web-based application, has been developed to easily analyze and investigate intervention effects of the SCED data at an individual level, but also to combine the SCED data through multilevel modeling and randomization tests, which create a higher internal validity (48). Randomization test are based on the random determination of the moments of phase change points to test a null hypothesis about treatment effects (85). Randomization tests have the advantage of being valid for single-case experiments without making distributional assumptions, of being easy to apply and of being extremely versatile for even the most complex single-case design.

Each SCED will be individually analyzed, but we will use *p*-value combining (of the 10 SCEDs in this project), which has the advantages that it is broadly applicable and that it is distribution-free without converting the scores to ranks or signs. The following schedule will be used to investigate when treatment effects occur during the study period:

The baseline data (phase A) will be compared with the intervention, post-intervention and follow-up data (phase B + C + D).The intervention data (phase B) will be compared with the baseline data (phase B) and with the post-intervention and the follow-up data (phase C + D).The post-intervention data (phase C) will be compared with the baseline data (phase A) and with the follow-up data (phase D).The follow-up data will be compared with the baseline data (phase A) and the intervention data (phase B).

A *p*-value of 0.05 will be set.

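### Seven diary phase contrasts share one 0.05 level with none named primary, and the intervention-versus-baseline contrast is printed as phase B against phase B

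*Protocol article*

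**What the plan says.** Section 2.10 (Statistical analysis) analyses each participant's diary separately, combines the p-values over the 10 participants, and gives a schedule of comparisons intended to show when effects occur:

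- "The baseline data (phase A) will be compared with the intervention, post-intervention and follow-up data (phase B + C + D": one contrast, A–BCD.
- "The intervention data (phase B) will be compared with the baseline data (phase B", continued by "and with the post-intervention and the follow-up data (phase C + D": two contrasts, B–baseline and B–CD. The baseline in the first carries the label of the treatment phase.
- "The post-intervention data (phase C) will be compared with the baseline data (phase A) and with the follow-up data (phase D": two contrasts, C–A and C–D.
- "The follow-up data will be compared with the baseline data (phase A) and the intervention data (phase B": two contrasts, D–A and D–B.

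The only statement on error is that a p-"value of 0.05 will be set". The questionnaires have separate paired tests.

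Section 2.4 (Measurement and outcome) lists disability (PDI, SFN-RODS) and QOL (SF-12) as main endpoints, with pain intensity, catastrophizing, mood and SFN complaints as secondary. It then says: "The primary endpoint is based on the clinical improvement of the participants". Section 2.5 (Daily measures) uses the diary for primary and secondary outcomes alike: "The diary is consisting of 9 questions about pain intensity, disability and physical activity, QOL and anxiety and depression". It does not say which items are primary.

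**The concern.** Section 2.9 states a hypothesis of effectiveness for disability and QOL, so the trial is framed as confirming an effect. A reader of section 2.10 cannot tell which comparison decides that hypothesis. Seven contrasts stand at equal rank under one threshold, and the primary endpoint sentence does not choose among them. A significant result on any baseline contrast, for any main-domain item, could be presented as showing effectiveness, and the chance of at least one such result from an ineffective treatment is above 5%.

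Section 2.9 says that the type I error of the randomization test is acceptable. That covers a single test, not a set of them. Combining p-values over participants leaves one result per item and contrast. It does not reduce the number of items or contrasts.

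The B-against-B label falls on the most direct comparison of treatment with baseline, so that comparison is undefined as printed.

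**Working it through.** The article gives no family-wise error figure, so there is none to reproduce.

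**Inputs from the article.** Seven contrasts and the 0.05 level (section 2.10); nine diary items (section 2.5; Table 2, offered as an example, shows seven); three main questionnaires (section 2.4); baseline of 10–30 days, treatment of 8 or 10 weeks, then two phases of two weeks (section 2.1).

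**Assumptions.** Phase lengths are 20 days (midpoint of 10 and 30), 63 days (9 weeks, midpoint of 8 and 10), 14 and 14. Days are independent, items have a common correlation between 0 and 0.9, and each contrast is a two-sided normal test at 0.05. The article does not state sidedness. B–baseline is read as B–A.

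**Expected false positives** (number of tests × 0.05, valid under any correlation):

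| Set of tests | Count | Expected |
|---|---|---|
| Two main-domain items × four baseline contrasts (A–BCD, B–A, C–A, D–A) | 8 | 0.40 |
| Nine items × seven contrasts | 63 | 3.15 |

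**Chance of at least one.** Independence would give 1 − 0.95^8 = 0.34 and 1 − 0.95^63 = 0.96. Independence cannot hold, because four phase means yield only three linearly independent differences. I therefore simulated the contrasts from shared phase means:

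| Set of tests | Item correlation 0 | 0.5 | 0.9 |
|---|---|---|---|
| Two items × four baseline contrasts | 24% | 22% | 17% |
| Nine items × seven contrasts | 86–87% | 72–73% | 41% |

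One item on all seven contrasts gives about 20%, against 1 − 0.95^7 = 0.30 under independence.

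**Questionnaires.** Three tests at one time point give at most 1 − 0.95^3 = 0.14 if independent, and less if correlated.

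**Which contrast the design supports.** Section 2.1 randomises the length of A and hence the start of B. Under section 2.2.3 the team sets the length of B from progress after four weeks. The changes from B to C and from C to D therefore have no random start point of their own, and B–CD, C–D and D–B lack the randomised basis that A–BCD has.

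**The case against.** The strongest reply is that this is a condensed article and that ranking of contrasts and multiplicity rules usually sit in an analysis plan that is not shown. That would answer a complaint about silence. Here, though, the article itself fixes the list of contrasts and a common level, and misprints one of them.

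Three further objections limit the size of the point, and they stand:

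- A reader might infer that the plan has no hierarchy at all. Section 2.4 does separate main from secondary domains, and section 2.9 states the hypothesis for disability and QOL only. Pain and mood items are not main-domain items.
- A reader might infer that several false positives are expected for the main objective, with a 96% chance of at least one. The article never says that every item is tested on every contrast. B–CD, C–D and D–B concern timing and maintenance, so significance there would not show benefit over baseline. The 96% also needs an independence that the contrasts cannot have.
- A reader might count 630 tests (63 × 10 participants). Section 2.10 combines p-values over participants, so these are not 630 separate claims.

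If tests are two-sided, about half of any false positives would point to harm. The B-against-B label is evidently a slip, since the same sentence calls it baseline and section 2.1 defines baseline as A. It does not affect the error rate.

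**Conclusion.** The point holds at moderate size. As written, section 2.10 leaves the deciding contrast open and section 2.4 does not supply it. On a charitable count (two main-domain items, four baseline contrasts), 0.4 false positives are expected and the chance of at least one is about 17–24%, three to five times the nominal 5%. On the broadest diary reading, 3.15 are expected and the chance is about 41–87%. The expected counts need no correlation assumption. The probabilities depend on the assumed phase lengths, independent days, two-sided tests and the item correlation. The documents do not establish the broad reading, so it is an outer bound and not the headline. The phase label needs correcting in any case.

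**What to change.** In section 2.10:

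- Name A versus B+C+D as the single primary diary contrast, because the randomised start of B supports it.
- Name two primary diary items, activity difficulty for disability and the daily life-score item for QOL. Test them with Holm at 0.05 overall (smaller p-value against 0.05/2 = 0.025, the other against 0.05).
- Keep PDI, SFN-RODS and SF-12 as main questionnaire endpoints, with Holm across the three (first step 0.05/3 = 0.0167) at one named time point.
- Report the other contrasts and items as timing or secondary analyses, with estimates and intervals.
- Correct the baseline label in the second comparison to phase A.

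Section 2.4 should point to these choices in place of its general sentence on clinical improvement. Since the diary and questionnaire families would each use 0.05, the text should also say which carries the effectiveness conclusion. If either alone would suffice, the joint error is bounded by 0.05 + 0.05 = 0.10.

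The cost is a short text change and a small loss of nominal power from Holm. No further participants or measurements are needed.

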### Study design

2.1

The design is a randomized replicated sequential single-case experimental ABCD design (SCED) with multiple measurements (48) (see Figure 1). Each participant will enrol in the baseline period, completing daily measurements with an electronic diary (A). The randomization in the baseline period will define the length of the baseline period (ranging between 10 to 30 days), increasing the internal validity and credibility (49, 50). By the randomization, the start point of the treatment module (date) will be determined (B). Therefore, the start point differs among participants (48, 51, 52). The treatment module will have a duration of 8 or 10 weeks, independent of the treatment type (these logistics are a standard clinical procedure). Each participant will be evaluated by the treatment team according to their personalized goals after 4 weeks. The further treatment module will exist of a short- (4 weeks) or long (6 weeks) treatment module, which will be added to the previous 4 weeks. The content of the short- and long treatment module will not differ. The only difference is the duration between both treatment modules. The differences between the short- and long treatment module will not be analyzed, because that is not the main focus of this study. After the treatment module, a post-treatment of two weeks will follow (C). At last, the study will end with a period two weeks of follow-up (D). Before the start of each period, participants will complete a couple of questionnaires (see Non-daily measures). The length of the baseline period (A) will be randomized between 10–30 days and participants will complete daily measurements with an electronic diary in the baseline period (A), for 8–10 weeks in the treatment module (B), two weeks post-treatment (C) and two weeks at follow-up (D) (see Figure 1, see Daily measures). Before the start of each period, participants will complete a couple of questionnaires (see Non-daily measures). Randomization of the baseline period will occur according to the length of the baseline period (between 10 and 30 days) and the start of the treatment module (B), increasing the internal validity and credibility (49, 50).

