### Sample size calculation

2.9

Based on previous experience with single-case experimental designs in chronic pain, 10 participants provide sufficient power to answer our hypothesis that rehabilitation based on biopsychosocial principles is effective to decrease disability and improving QOL (79). Therefore, at least 10 participants need to complete the study. In case a participant withdraws, a new participant will be included. Studies that tested the statistical properties of the randomization test used in this type of design showed that type I error probability of the randomization test was maintained at an acceptable level (48, 80, 81). SCED studies have multiple measurements, resulting in a large effect size and great power (82). Each participant is equal to one experiment. And each experiment will be repeated at least for 10 times. The variation of the treatment starting point will show if a treatment is effective, and that the significant outcome is related to the treatment modality. With a kind of meta-analysis, it is possible to combine all the *p*-values (of each participant). Therefore, this study design is a powerful method due to the multiple measurements and the number of participants (10 repetitions). Compared to RCT studies, more than 100 participants will be included, with only a couple of measurements per participant. Contrary to SCEDs, daily and multiple measurements will be gathered, and therefore, a sample size of 10 is enough to analyze the data with a sufficient outcome. The total number of participants and permutations is not related to the power of the design, however, calculation of the p-value is possible by dividing the total number of permutations (83). The aim of this study is to observe if a multidisciplinary rehabilitation treatment modality is suitable and effective in the treatment of psychosocial factors in SFN. certain treatment modalities are used as care as usual in different chronic pain conditions, in which there is always a selection between different treatment options.

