It is important that the various periods [ea. (A), (B), (C), (D)] show a substantial amount of non-overlapping data. Nonoverlapping data of pairs (NAP) is an indicator of differences between the different phases in the treatment schedule. We do not expect that there will be an immediate effect from the start of treatment, however, we expect that there will be a gradual positive effect.

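### The diary data are tested with a start-date randomisation test suited to an abrupt effect, although the plan expects a gradual one; the claim of sufficient power is unsupported for slow improvement

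*Protocol article*

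**What the plan says.** Section 2.1 (Study design) randomises one thing, the length of the baseline: "The length of the baseline period (A) will be randomized between 10–30 days". Treatment then lasts 8 or 10 weeks, followed by two weeks of post-treatment and two weeks of follow-up with the daily diary.

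Section 2.10 (Statistical analysis) analyses the diary with randomisation tests based on the randomly determined phase-change points. P-values are combined over the 10 participants. The first listed comparison is of whole phases: "The baseline data (phase A) will be compared with the intervention, post-intervention and follow-up data (phase B + C + D"). The non-overlap measure NAP is described as an indicator of differences between phases. The section then says: "We do not expect that there will be an immediate effect from the start of treatment", and that a gradual positive effect is expected instead.

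Section 2.9 (Sample size calculation) says that "10 participants provide sufficient power to answer our hypothesis", and bases this on the many daily measurements, the ten replications and the random start: "The variation of the treatment starting point will show if a treatment is effective".

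**The concern.** A start-date randomisation test asks whether the phase difference at the true start date is larger than at the other dates that could have been drawn. It has power only if the true date stands out. A jump in level makes it stand out. A slow rise need not: moving the supposed start later puts a few early treatment days, still close to baseline, into the baseline phase and raises the mean of what follows. The difference can then be larger at a wrong, later date.

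The possible dates span only 21 days, while treatment runs for 56 or 70. If improvement takes most of that time, the p-value says more about which date was drawn than about whether treatment worked. The diary result could then be non-significant for a treatment that works as the investigators expect. More diary days do not by themselves cure this, although section 2.9 relies on them.

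**Working it through.** **Plan's own figure.** Section 2.9 gives no power percentage, effect size, within-person SD or autocorrelation, so there is nothing to reproduce.

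**Inputs from the article.**
- 10 participants.
- Baseline 10–30 days, read as 30 − 10 + 1 = 21 equally likely start dates. The smallest one-participant p-value is 1/21 = 0.048.
- Phase B of 56 or 70 days; C + D of 14 + 14 = 28 days.
- Significance level 0.05.

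**Assumptions, because the article is silent.**
- Statistic: mean(B+C+D) − mean(A).
- One-sided testing.
- Edgington's additive combining rule.
- C and D contiguous with B.
- AR(1) noise with lag-1 autocorrelation 0, 0.3 or 0.5.
- Effects expressed in within-person SD.

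**Step 1: one participant, no noise.** Take a true baseline of 20 days, B = 56 days, and an effect rising linearly to 1 over B, so that treatment day j has effect j/56. The effects sum to 28.5 over B and 28 over C + D, in total 56.5.
- True date (20): 56.5/84 − 0 = 0.673.
- Date 10: 56.5/94 − 0 = 0.601.
- Date 30: the first 10 treatment days, with sum 55/56 = 0.982, fall into the baseline. The difference is (56.5 − 0.982)/74 − 0.982/30 = 0.750 − 0.033 = 0.718.

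The later date beats the true one. Over all 21 dates the difference peaks at day 30 for true starts of 15 or later, and at day 23 for a start on day 10. For true starts 10, 15, 20, 25 and 30 the p-value is (31 − start)/21 = 1.00, 0.76, 0.52, 0.29 and 0.05. It follows the drawn date.

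With an immediate shift of 1 and a true start of 20, the true date gives 1, date 10 gives 84/94 = 0.894, and date 30 gives 1 − 10/30 = 0.667. The true date wins and p = 1/21.

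**Step 2: combining rule.** Each p-value is rank/21. Edgington's rule gives 0.048 at a rank sum of 73 and 0.053 at 74, so it rejects at 73 or less. With only 21 dates the true size is then 2.8%. Using the exact discrete null, the cut-off is 77 and the size 4.5%.

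**Step 3: combined power by simulation.** There were 20,000 simulated trials per cell, so the Monte Carlo standard error near 5% is √(0.05 × 0.95/20,000) = 0.15 percentage points. Power in %, Edgington rule, at autocorrelation 0 / 0.3 / 0.5:

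| Time course | Final effect 1 SD | Final effect 2 SD |
|---|---|---|
| Immediate | 95.5 / 87.0 / 78.4 | 100.0 / 99.8 / 99.2 |
| Rise over 14 days | 27.0 / 18.6 / 14.8 | 68.8 / 51.5 / 40.1 |
| Rise over 28 days | 9.2 / 7.9 / 6.6 | 20.1 / 14.7 / 12.6 |
| Rise over 56 days | 5.1 / 4.3 / 3.5 | 7.2 / 6.1 / 5.7 |
| Rise over 70 days | 4.3 / 4.0 / 3.8 | 6.1 / 5.6 / 4.8 |
| 14-day lag, then 42-day rise | 2.2 / 2.2 / 2.7 | 1.7 / 2.0 / 1.9 |

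At 0.5 SD, an immediate shift gives 57 / 42 / 32% and a full-length rise 3.1–3.7%.

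**Step 4: other readings of the test.**
- Exact null: 5.0–10.7% for the full-length rise (0.5–2 SD). For a 7-day rise, 43–70% at 1 SD and 88–99% at 2 SD.
- 56-day rise, two-sided with exact null: 4–11%.
- 56-day rise, NAP as the statistic: 5–6% (Edgington) or 7–9% (exact null).
- 56-day rise, A versus C+D: 4–6% at 1 SD and 7–13% at 2 SD (Edgington).

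**The case against.** A reader might infer that the planned test cannot detect any gradual effect, or that its power is 2–7% without qualification. The documents do not support either. They say only that the effect is gradual, without a speed. A rise complete in one or two weeks is also gradual, and there power runs from about 15% to 99%. Part of the lowest figures also comes from the assumed combining rule, which is conservative with 21 dates. The statistic, rule and sidedness may stand in an analysis plan that is not shown, so their absence is no fault here.

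A reader might also infer that the whole trial would report no effect of a working treatment. That does not follow. Section 2.4 names the PDI, SFN-RODS and SF-12 as measures of the main endpoints, and section 2.10 analyses the questionnaires with paired tests, which do not depend on the start date. Nor does the article call A versus B+C+D the main test; it is the first of several comparisons meant to show when effects occur.

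All of this stands, and it limits the figures and the consequence. The conflict remains, because the comparisons, the expected time course and the power claim are all stated in the article. Section 2.5 says that the diary measures primary and secondary outcomes, and the power argument in section 2.9 rests on this test. Multilevel modelling is mentioned only as something the application can do. No lag, slope or trend comparison is given.

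**Conclusion.** The point holds in conditional form. The claim of sufficient power can be true for an immediate shift of about 1 SD (78–96%), which is the shape the investigators do not expect. If improvement builds over the full 8–10 weeks, power is little above the size of the test: about 3–7%, or 5–11% with the exact null. It is lower still after a two-week lag. For 1–2 SD it is about 7–20% with a 4-week rise and 15–69% with a 2-week rise.

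The figures rest on the stated assumptions about statistic, sidedness, combining rule, autocorrelation and effect size. The direction does not depend on the noise: step 1 shows it without any. The statement that the varying start will show whether treatment works is therefore not justified for slow improvement. A non-significant diary result could not be read as absence of effect.

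**What to change.** 1. **Section 2.9.** Limit the power claim to an abrupt or near-abrupt shift of a stated size. Say that power for a slow gradual effect is low, and show the range by duration of rise.
2. **Section 2.10.** For the randomisation test, pre-specify a gradual-effect statistic (a ramp or slope change), with its shape fixed from the expected time course and recomputed at each possible start date. Keep the whole-phase mean and NAP comparisons as secondary. This preserves the distribution-free inference that the article gives as its reason for the method.
3. **Optional.** Add a supportive multilevel piecewise model with AR(1) errors, reporting the pooled slope change with a 95% confidence interval. It needs participant-level random trends and slope changes. Without them, in a simulation with no treatment effect (1,500 trials per cell) and participants' linear trends varying with SD 1 over 80 days, two-sided type I error was about 12 / 9 / 8% at autocorrelation 0 / 0.3 / 0.5. With no trend variation it was 5–6%.

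**Cost.** Analysis wording and modest programming; recruitment, treatment and data collection do not change. The gain is partial. For an 8-week rise, a matched ramp statistic gives about 16–24% power at 1 SD and 44–68% at 2 SD (Edgington; autocorrelation 0.3 and 0). It also depends on the assumed shape, and the power that can honestly be stated becomes less favourable.
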